### Sample size

Previous data indicate the intraclass correlation coefficients (ICC) for alcohol consumption in the last 30 days at community and school levels were .01 and .05, respectively. We calculated the required sample with power 0.8, type I error 0.05 and design effects based on clustering effect (ICC) at community, school and classroom clustering ranging from 0.1 to 0.01. Recent Australian secondary school survey data [10] indicate rates of alcohol use in the past month were 22% in grade 8 (average age 14) and 48% in grade 10 (age 16) (combined average 35%). Assuming 65% of parents consent to their child participating, we will request informed consent from 5400 to recruit 3500 students in 2017 (wave 1). These cohorts will be resurveyed at two time points after the intervention is delivered. Assuming an 80% retention rate, the hypothesised 15% reduction can be detected with 2800 participants in the longitudinal analyses. The research team will work with communities and relevant stakeholders to recruit schools for the study. Primary outcome data will be collected in the school setting using the CTC youth survey.

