## Background

Community-led interventions that systematically and strategically implement evidence-based programs have been shown to be effective in producing population-level behaviour change, including reduced alcohol and drug use. Australian guidelines recommend that adolescents should not consume alcohol before they are 18 years but 44% do, with 34% reporting use in the last 30 days [1]. Community interventions such as the “Communities That Care” prevention framework have the potential to reduce these adolescent alcohol consumption (CTC; [2–4]. The CTC framework can be used to mobilise community stakeholders and organise them to work strategically to prevent the development of harmful behaviour patterns. Communities are supported to utilise local data to identify priorities and then to plan the implementation of interventions that have been found to be effective in previous evaluations.

Large community trials in the United States of America (USA) reveal that CTC can increase community implementation of evidence-based prevention interventions and reduce health-risk behaviour patterns among teenagers, resulting in reductions of between 15% - 25% in the prevalence of youth problems [2, 4]. Economic evaluations also indicate that CTC is worthwhile investment. Conservative estimates suggest CTC can produce a return on investment of approximately US$10.23 for every dollar [5, 6]. Over ten years, pilot work developing CTC in Australia has facilitated recruitment and training of community coalitions to plan and implement evidence-based programs. This work has demonstrated feasibility of CTC in Australia. Pilot studies have shown the CTC approach has been successfully implemented with fidelity and has been associated with reductions in teenage alcohol and drug use in line with those achieved in the USA (i.e. 15%) [7]. This study will employ a Type II translational randomised control trial to evaluate the effectiveness of CTC in Australia.

The primary outcome will be the proportion of secondary school age adolescents who use alcohol before the Australian legal purchasing age of 18 years. Based on pilot work done in Australia and CTC trial work done in the USA, we hypothesise that: compared to control communities, participants in intervention communities will maintain at least a 15% lower rate of frequent (last 30 days) youth alcohol use throughout the secondary school age period (primary outcome).

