**Fig. 1 Fig1:**
[figure not shown]
Flow chart estimating the progress of communities, schools and participants through trial. Trial registration: ACTRN12616001276448. *Wave 1 will be with either year 8 & 10, or Year 9 and 11, depending on speed in which communities work through the CTC phases, and the ease in which ethics is approved in the relevant school jurisdictions, and thus when the subsequent collection of survey data can occur. Final wave will be with year 11 students and 1 year post school. ** Approximate estimate of sample size of longitudinal cohort after 80% retention rate

Two secondary schools from each of the 28 communities will be invited to participate. Informed consent of school leaders will be required for school participation and if a school declines a nearby school will be approached. The survey will include items that assess alcohol use, and other related-behaviours as well as risk and protective factors (see measures below).

Students in the participating schools will be invited to complete the survey if they satisfy the following inclusion criteria:Are in the relevant (either Year 8 or 10) secondary school classroom grades (average age Grade 8 = 14 years; Grade 10 = 16 years);Have signed informed consent from their parents; andHave provided individual assent.

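### The claim of 80% power for a 15% reduction with 2,800 participants does not follow from the plan's own ICCs; 2,800 is close to the number needed with no clustering at all

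*Protocol article*

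**What the plan says.** The Sample size section gives the ICCs for past-30-day alcohol use "at community and school levels were .01 and .05, respectively". It then says: "We calculated the required sample with power 0.8, type I error 0.05 and design effects based on clustering effect (ICC") over a range from 0.1 down to 0.01, covering community, school and classroom. The control rate comes from survey figures of "22% in grade 8 (average age 14) and 48% in grade 10 (age 16) (combined average 35"%). With 3,500 students recruited, the section concludes: "Assuming an 80% retention rate, the hypothesised 15% reduction can be detected with 2800 participants in the longitudinal analyses".

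The cluster structure is given elsewhere. Under Participants and research eligibility: "Two secondary schools from each of the 28 communities will be invited to participate". Random allocation describes 14 matched pairs, with one community of each pair assigned to the intervention.

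The target effect is in the Background, where the hypothesis is that intervention communities will "maintain at least a 15% lower rate of frequent (last 30 days) youth alcohol use throughout the secondary school age period". The US trials are cited there as "resulting in reductions of between 15% - 25% in the prevalence of youth problems".

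**The concern.** The section says that the sample size includes design effects for clustering. Yet 2,800 is only slightly more than an individually randomised trial would need for this effect, and the school-level ICC of .05 with about 50 students per school is far from negligible.

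This is the only power statement in the article for the primary outcome. If the true power is well below 80%, a null result could be taken as evidence against the intervention when the trial may have had little chance of detecting the target effect.

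**Working it through.** **Inputs.** Control rate 35%, ICCs .05 and .01, power 0.8, type I error 0.05 and 2,800 analysed (Sample size). 28 communities with two schools each (Participants and research eligibility). Equal allocation (Random allocation). The 15% is read as relative, because the Background speaks of a lower rate and of reductions in prevalence; this gives 29.75%. A two-sided test is assumed, since the section does not state sidedness.

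**What reproduces.** 5,400 × 0.65 = 3,510; 3,500 × 0.80 = 2,800; (22 + 48)/2 = 35. The 80% power does not reproduce, as follows.

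**1. Without clustering.** n per arm = (1.96 + 0.8416)² × (0.35 × 0.65 + 0.2975 × 0.7025) / 0.0525² ≈ 1,243, or 2,486 in total. The pooled-variance version gives 2,492, and 2,568 with continuity correction. The room left for clustering is 2,800 / 2,486 = 1.13. Power at 2,800 with clustering ignored is 84%.

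**2. Cluster sizes.** 2,800 / 56 schools = 50 per school; 2,800 / 28 communities = 100 per community.

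**3. Design effect (DE).** DE = 1 + (50 − 1) × ICC(school) + (100 − 50) × ICC(community).
- .05 as the total within-school correlation: 1 + 49 × .05 + 50 × .01 = 3.95.
- .05 and .01 as additive components: 1 + 49 × .06 + 50 × .01 = 4.44.
- Community ICC .01 only: 1 + 99 × .01 = 1.99.

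**4. Power, single post-intervention comparison, 35% v 29.75%.** At DE 3.95 the effective total is 2,800 / 3.95 = 709, SE = √[(0.2275 + 0.2090) × 3.95 / 1,400] = 0.0351, z = 0.0525 / 0.0351 = 1.50.

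| DE | Effective N | Power, normal | Power, t (26 df) | Power, t (13 df) |
|---|---|---|---|---|
| 1.99 | 1,407 | 56% | 53% | 50% |
| 3.95 | 709 | 32% | 30% | 28% |
| 4.44 | 631 | 29% | 27% | 26% |

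A one-sided test gives 44% and 41% (normal) at DE 3.95 and 4.44.

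**5. Detectable relative reduction at 80% power, 35% control rate.** 27.5% (normal) or 28.5% (t, 26 df) at DE 3.95; about 29% (normal) at DE 4.44.

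**6. Grade 10 rate of 48% (48% v 40.8%).** At DE 3.95, SE = √[(0.2496 + 0.2415) × 3.95 / 1,400] = 0.0372 and z = 0.072 / 0.0372 = 1.93, so power is 49% (normal) or 46% (t, 26 df). At DE 4.44 it is 45% (normal). The detectable reduction at DE 3.95 is about 22%.

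**7. Credit for longitudinal data (assumed; not in the article).** Suppose baseline adjustment and the mean of two follow-ups. Each variance component is then multiplied by (1 + r)/2 − r², where r is its correlation over time. DE 3.95 splits into 3.00 between clusters and 0.95 within.
- 35% control rate, cluster r from 0.5 to 0.8 and within-person r from 0.3 to 0.5, under either reading of the ICCs: power about 50–76% (normal). With cluster r of 0.9 it exceeds 80%.
- 48% control rate, cluster r 0.7, within-person r 0.4: 3.00 × 0.36 + 0.95 × 0.54 = 1.59, giving power of about 86% (normal) or 83% (t, 26 df).

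At 35%, reaching 80% needs the variance cut to 1.126 / 3.95 = 29%, or 1.126 / 4.44 = 25%, of its single-wave value.

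**The case against.** The strongest objection is that a single cross-sectional contrast is not the planned test. The claim is made for the longitudinal analyses. Participants and research eligibility sets out a baseline and two post-intervention waves, Statistical analyses tests time-by-treatment interactions, and communities are matched in pairs. Also, 35% is an enrolment-age rate. The Abstract puts the mean age at 19 by 2021, and the note to Fig. 1 places the final wave in Year 11 and one year after school, so the control rate at follow-up may well be higher.

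This stands, and it rules out two stronger readings that a reader might infer. The first is that the trial's real power is about 30%. The documents support that figure only for one post-intervention wave at 35%; step 7 shows that power could reach 80% under favourable assumptions. The second is that the detectable effect lies beyond the 15–25% range cited from the US trials. That holds at 35% but not at 48%, where it is about 22%.

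The objection does not rescue the stated claim. The section uses 35% and gives no correlation over time and no follow-up prevalence. Nor is this a complaint about brevity in an article: the result and its inputs are both printed, and they disagree.

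Reading the 15% as percentage points (35% to 20%) would give about 99% power even with clustering. But that is a 15/35 = 43% relative reduction, which does not fit the Background.

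**Conclusion.** Wrong as written. The stated power of 0.8 with clustering allowed for does not follow from the stated prevalence, ICCs, cluster numbers and 2,800 participants. The sample allows a design effect of about 1.13, while the stated ICCs imply 3.95 to 4.44. Even the smallest stated ICC, applied at community level alone, leaves a single-wave comparison at about 53–56% (normal or t with 26 df).

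The conclusion rests on the relative reading of 15%, a two-sided test and equal cluster sizes. A one-sided test does not change it. The power of the planned longitudinal analysis cannot be determined from the article.

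**What to change.** Do not enrol more students. Withdraw the 80% statement and restate power and detectable reduction from the stated ICCs and cluster sizes. Suggested wording:

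*With 28 communities, 56 schools, 2,800 retained participants and ICCs of .05 (school) and .01 (community), the design effect is about 3.95. For a single post-intervention comparison at a control rate of 35%, power for a 15% relative reduction is about 30%, and the relative reduction detectable with 80% power is about 28%.*

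If the authors rely on baseline adjustment, repeated waves or higher prevalence at follow-up, they should add the correlations and prevalence used and the power that results. They should also say whether the two ICCs are nested or additive, whether the test is two-sided, and that 15% is relative.

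The cost is a rewritten section and a less favourable stated power. Design and recruitment do not change.

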### Survey measures

Survey measures will be based on validated measures of behaviours and validated risk and protective factors [11] and archival data. The survey instrument has been used in large CTC trials in the USA and Australia [12]. More information about the survey instrument can be found here (https://www.communitiesthatcare.org.au/5-phases-ctc). Example questions are provided below. Primary outcome data in control and intervention sites will be collected in the school setting using the CTC youth survey.

### Primary outcome measure

*Alcohol use in the last 30 days:* “In the past 30 days have you had more than just a few sips of an alcoholic beverage (like beer, wine, or spirits) (yes/no)?” This measure has been validated in surveys and community trials [1, 13, 14].

### Secondary outcomes

Survey data will also be used to assess a series of secondary outcomes.

*Alcohol risk and harm*: recent risky drinking: “Think back over the past 2 weeks. How many times have you had five or more alcoholic drinks in a row?”

*Alcohol use disorders* will also be investigated using questions from the Alcohol Use Disorders Identification Test (AUDIT) [15].

*Intention to drink before 18:* National Australian guidelines recommend that adolescents should avoid alcohol before the age of 18; students will, therefore, be asked about intention to use alcohol before the age of 18: “I do not intend to consume alcohol before I am 18 years of age (yes/no)?”

*Illicit drug use:* “In the past 30 days, have you: Used marijuana (pot, weed, grass)?; Used other illegal drugs (like cocaine, heroin, ecstasy, or amphetamines/speed?”

*Tobacco use:* Lifetime, past year and past 30 days assessments will be made. For example, “In your lifetime have you ever smoked cigarettes?”

*Antisocial behaviour/violence/offending:* “How many times in the past year (12 months) have you: Beaten up someone so badly that they probably needed to see a doctor or nurse?” and “Stolen something worth more than $10?”

*Secondary school engagement:* Will be measured with scales assessing school commitment, academic performance, and attendance. School completion will be based on successfully completing secondary school.

*Depression*: The short mood and feeling questionnaire (SMFQ) will be used to measure adolescent depression [16].

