### Participants and research eligibility

The primary hypothesis will be tested using a longitudinal school survey. Three waves of data will be collected; pre-intervention (baseline), and two waves post-intervention (see Fig. 1, Flow diagram).

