### Statistical analyses

Intention-to-treat analyses will be employed. To account for within-individual variation we will employ repeated measures models with split-plot in time design matrix with binary outcome and logit link. Model parameters will be estimated using generalised estimating equations (GEEs) accounting for correlation within participants with an exchangeable working correlation matrix. For continuous secondary outcomes, GEEs with a Gaussian distribution and identity link will be implemented.

To assess the impact of the intervention on primary and secondary outcomes, time by treatment interactions will be examined in a model that includes the fixed categorical effects of assessment time, group indicator and treatment by group interaction. Trend effects due to staggered rollout of the intervention will be assed using models with a fixed effect categorical factor for year of treatment.

Clustering effects for schools and communities will be evaluated by calculating ICC and, if necessary, a series of (generalised) linear mixed models accounting for *clustering* (within participant/class/school/community). Analysts will not be blind to the communities that have been allocated to either intervention or control.

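### Lifetime tobacco use cannot revert, so the logit time-by-treatment interaction measures its change less directly and less precisely than initiation among wave-1 never-smokers (low-priority improvement)

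*Protocol article*

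**What the plan says.** Under Secondary outcomes, tobacco use is measured over three recall periods: "Lifetime, past year and past 30 days assessments will be made". The one item worded there is the lifetime one: "In your lifetime have you ever smoked cigarettes".

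Under Statistical analyses, the binary-outcome method is "repeated measures models with split-plot in time design matrix with binary outcome and logit link", fitted by GEE with an exchangeable working correlation within participant. The test is common to all outcomes: "To assess the impact of the intervention on primary and secondary outcomes, time by treatment interactions will be examined". The only variation by outcome type is a Gaussian, identity-link version for continuous outcomes.

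Baseline is one of the time points, since under Participants and research eligibility "Three waves of data will be collected; pre-intervention (baseline), and two waves post-intervention".

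The article does not restrict the lifetime item to students who had never smoked at wave 1, and it does not define smoking initiation as an outcome.

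**The concern.** A lifetime item is absorbing: a student who answers yes at wave 1 is yes at waves 2 and 3 whatever the intervention does. Only students who answered no at wave 1 can show an effect. A model built for outcomes that move both ways therefore does two unhelpful things here.

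- Its interaction odds ratio mixes the effect on initiation with the level of baseline ever-use. The same effect on initiation gives a different odds ratio in a population with a different smoking history.
- The contrast is a change in log-odds, so it carries the sampling noise of baseline prevalence, which an analysis of initiation does not.

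At stake are the interpretability and precision of one recall period of one secondary outcome.

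**Working it through.** **Inputs from the article.** Planned longitudinal sample: 3500 × 0.80 = 2800, so about 1400 per arm. From Sample size: "We calculated the required sample with power 0.8, type I error 0.05" (taken as two-sided). Effect: the 15% reduction hypothesised for alcohol, applied here to smoking initiation as an assumption. The article gives no power figure for tobacco, so there is none to reproduce.

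**Assumed inputs.** The article gives no tobacco rates and no tobacco ICC. Baseline ever-use p0 is varied over 10–40% and control-arm initiation q by the last wave over 10–30%. Clustering is left out at first.

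**1. What the interaction estimates.** Ever-use at follow-up is p1 = p0 + (1 − p0)q. Follow-up odds divided by baseline odds are

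[p0 + (1 − p0)q] / [p0(1 − q)],

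which depends on p0 even when q is fixed. Take q = 20% in control and 0.85 × 20% = 17% in intervention. Among never-smokers the odds ratio is (0.17/0.83)/(0.20/0.80) = 0.82. The interaction odds ratio for that same effect is 0.87 at p0 = 10%, 0.90 at p0 = 20% and 0.93 at p0 = 40%.

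**2. Chance baseline imbalance.** Let q = 20% in both arms, so there is no effect, with p0 = 20% in one arm and 25% in the other. The ratios are 0.36/(0.20 × 0.80) = 2.25 and 0.40/(0.25 × 0.80) = 2.00, so the interaction odds ratio is 2.00/2.25 = 0.89. This is conditional on that imbalance. In a simulation of 14 v 14 communities of 100 (assumed ICC 0.03, 3,000 runs, t-test on community summaries standing in for a clustered model), both analyses held about 5% type I error. The imbalance is therefore noise already reflected in the standard error, not bias.

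**3. Precision.** For an absorbing item the within-person covariance is p0(1 − p1). By the delta method, with n students per arm, the variance of the logit change in one arm is

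[1/(p1(1 − p1)) + 1/(p0(1 − p0)) − 2/(p1(1 − p0))] / n.

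The comparator is initiation among the n(1 − p0) wave-1 never-smokers per arm.

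Worked case, p0 = 10%, q = 20% v 17%, n = 1400:
- Interaction: p1 = 0.280 v 0.253; difference in log-odds 0.138; SE = √[(8.135 + 7.619)/1400] = 0.106; z = 1.30; power 26%.
- Initiation: 1260 per arm; difference in log-odds 0.199; SE 0.103; z = 1.94; power 49%.

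| p0 | q | Interaction | Initiation | Information kept by interaction |
|---|---|---|---|---|
| 10% | 20% | 26% | 49% | 45% |
| 20% | 20% | 32% | 45% | 68% |
| 20% | 30% | 46% | 66% | 61% |
| 40% | 20% | 32% | 35% | 88% |

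A simulated three-wave exchangeable GEE (120 runs per setting) agrees: 27% v 48% at p0 10%, q 20%, and 53% v 68% at p0 20%, q 30%.

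**4. Where the loss comes from.** The share of follow-up positives that predate the intervention is p0/p1. At p0 40%, q 10% it is 0.40/0.46 = 87%, yet power is 18% v 19%. At p0 10%, q 30% it is 0.10/0.37 = 27%, and power is 34% v 71%. The loss is thus greatest where earlier smoking is rarest. On the risk-difference scale the same change contrast nearly matches initiation: 48%, 43% and 33% at q = 20% with p0 = 10%, 20% and 40%, against 49%, 45% and 35%. The loss comes mainly from the logit change contrast with a noisy baseline prevalence.

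**5. With clustering.** Halving to 700 per arm (design effect about 2) gives 15% v 28% at p0 10%, q 20%, and 19% v 25% at p0 20%, q 20%.

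**The case against.** The strongest case against the point has five parts.

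- **Earlier smoking is not credited to either arm.** Baseline is in the model, so earlier smoking is largely netted out. This stands. A reader might infer that old smoking is recounted as an intervention outcome and that this destroys the power. The documents do not support that reading: the model includes wave 1, and step 4 shows the loss shrinking as the share of earlier smokers grows.
- **Type I error is held.** This also stands. A reader might take the 0.89 under no effect as bias, but it is ordinary sampling variation given a chosen imbalance.
- **The size rests on assumed rates.** True. The gain is large at baseline ever-use of about 20% or less and small at 40%. With clustering and a 15% reduction, neither analysis exceeds 43% power over the assumed range, so the change does not make this outcome well powered.
- **Little of the trial is touched.** True. Past-year and past-30-day tobacco use can move both ways. The article states no initiation hypothesis, and its primary outcome is alcohol use.
- **The detail belongs in an analysis plan.** This stands only in part. How each recall period becomes a variable could be settled there. But the article does state one method for binary secondary outcomes, and read as written it covers the lifetime item.

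**Conclusion.** The point holds as a low-priority, cheap improvement, not as a validity error. For the lifetime tobacco item the interaction odds ratio is not the effect on initiation, and it was less efficient than an initiation analysis in every setting tried. Over p0 10–40% and q 10–30%, the efficiency of initiation relative to the interaction runs from 1.08 to 2.62. At 1400 per arm that is a gain of 23 power points at p0 10%, q 20%, 13 points at 20%, 20%, and 3 points at 40%, 20%.

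These sizes rest on assumed smoking rates, a 15% reduction borrowed from the alcohol hypothesis, and no clustering. It would go too far to say that much of the power is lost whatever the smoking rates: the article gives none, and at 40% baseline ever-use the loss is slight. The direction does not depend on which of the assumed rates is taken.

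**What to change.** Add one sentence to Statistical analyses: lifetime tobacco use will be analysed as initiation by each follow-up wave among students who answered 'never' at wave 1, comparing arms with the same allowance for clustering as the other outcomes. Keep the time-by-treatment interaction for past-year and past-30-day tobacco use.

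No new data are needed, because the cohort survey already yields the wave-1 answer. The costs are:
- Baseline ever-smokers, who cannot initiate, leave this one analysis.
- So do students without a wave-1 answer.
- Smoking begun between wave 1 and delivery is still counted as initiation. Table 1 places the first survey in 2017/18 and both listed interventions in 2018/19, so this gap may matter and should be acknowledged when the result is reported.
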